### Randomization and blinding

To ensure balanced groups throughout the enrollment period, randomization will be conducted using a permuted block procedure, with block sizes varying between 4 and 6, depending on the number of eligible parents. To ensure allocation concealment, the sequence will be generated through computer randomization software by an independent researcher not involved in participants’ enrollment or assessments. Group assignments will be further communicated to the research team, who will subsequently inform parents of their allocation via telephone. Additionally, groups’ equivalence will also be assessed regarding primary outcomes and key covariates. Considering the nature of the intervention and similarly to research evaluating TIK in other countries (e.g., [48]), this study will be an open-label trial, as neither the researchers nor the parents will be blinded to the participants’ group allocation.

### Patient and public involvement

Community partners will be involved in the design, conduct, and reporting of the trial. At a developmental stage, stakeholders will provide advice about effective recruitment strategies and dissemination plans, as well as anticipated barriers to recruitment and efforts to overcome them, to maximize successful participants’ engagement. During the implementation phase, stakeholders will lead the recruitment of participants through general dissemination channels and personalized referrals, and periodic meetings will be held to monitor the impact of the recruitment strategies. Community partners will also provide facilities for group sessions. The trial’s results, namely those related to process evaluation, will be discussed with the stakeholders to determine whether changes (and which) to TIK should be made to optimize its integration into routine, integrated care. At the midpoint of the project, one seminar directed to community partners will be held to monitor implementation of the project and make appropriate adjustments, if necessary, as well as to provide preliminary results. Tools for disseminating the trials’ results among the general public will also be co-created with community partners.

### The intervention

#### Tuning in to Kids^®^ Intervention

Tuning in to Kids^®^ is an evidence-based parenting program for children aged 3 to 12, designed to foster emotionally responsive parenting, thereby promoting children’s emotional development. Drawing upon research in the field of emotion socialization (e.g., [49, 50], the program is based on the premise that children’s MH difficulties can be reduced through the experience of emotional validation by parents. The TIK program is delivered as a structured, group-based intervention consisting of six 2-hour weekly in-person sessions [9]. A follow-up booster session is included in the program to allow parents to consolidate their learning and address current main challenges. The sessions are conducted by two facilitators in closed groups of 8 to 12 parents. After session 2, no additional participants were allowed to join the group, to facilitate peer support and open discussion. Program content combines psychoeducation, group brainstorming, role-play exercises, video materials, and home practice activities for parents to apply emotion coaching in real-life scenarios. The structured format (see Table 2) provides a supportive environment for parents to reflect on their own meta-emotion and progressively develop the skills to respond to their child ren’s emotions through emotion coaching [51]. More information about the program can be found at the website: https://tuningintokids.org.au/. The Portuguese version of TIK was adapted primarily to ensure linguistic and cultural relevance (i.e., after being translated into Portuguese, the materials were reviewed for cultural appropriateness). Only minor modifications were made, including the adaptation of some examples and references in the program content to better reflect Portuguese family contexts.

**Table 2 Tab2:** Session-by-session description of the Tuning in to Kids^®^ intervention

Session	Themes
1	Introducing the program and the concept of emotion coaching, while creating a warm, non-judgmental environment that normalizes parental challenges and worries, builds emotional awareness, and welcomes participants.
2	Exploring emotion coaching and the concept of meta-emotion by helping participants to reflect on how past experiences with the family of origin and cultural values influence parenting practices and the use of empathetic responses.
3	Supporting parents to understand children’s emotional experiences around sadness by responding with empathy and validating feelings to promote emotional regulation.
4	Consolidating skills in self-care and responding to children’s fears during periods of heightened emotional activation.
5	Reflecting on children’s anger and parents’ own emotional self-regulation, to use emotion coaching to respond to challenging behaviors.
6	Consolidating learning by reviewing the program, reinforcing the five steps of emotion coaching and encouraging ongoing practice, self-care, and further growth.

Adapted from [52]

The group’s location, dates, and starting times will be determined according to participants’ preferences and availability and will be communicated to participants at least three weeks before intervention starts, followed by a reminder text message one day before the intervention begins. Participants will be able to discontinue study participation (1) upon request or (2) if the facilitators noticed some harmful effects (e.g., severe emotional activation). In such cases, participants will be asked if they want to receive another type of professional support and/or resources. Concomitant individual care for either parents or children is permitted during the trial. No new participants are admitted after the second session to ensure a safe and consistent group environment. Moreover, intervention groups will consist exclusively of parents enrolled in the trial.

To promote participant retention, when participants miss a session, facilitators will contact them by telephone to inquire about the underlying reasons for missed sessions and explore obstacles that may have hindered attendance. Wherever possible, the research team will provide solutions to overcome potential barriers and enhance participation (e.g., normalizing potential anxiety felt in a group intervention, providing childcare for siblings). Parents allocated to the waitlist control group will be regularly contacted throughout the waiting period by the research assistants, by telephone and SMS, to share updates on trial progress, and provide reminders of scheduled assessments and that they will receive the intervention after the follow-up assessment.

#### Training, supervision, and implementation fidelity

All facilitators will have at least a master’s degree in psychology and have completed the mandatory TIK professional training, being certified as TIK facilitators. The training program is designed to enhance knowledge and develop the essential skills for effective TIK delivery, thereby improving the qualification of TIK facilitators. Each facilitator will follow a standardized manual outlining specific procedures and activities for each session. Facilitators will receive supervision throughout delivery from the program authors (before session 1 and after sessions 2, 4, and 6) to enhance fidelity to the TIK program and give advice to overcome potential challenges (e.g., adherence to the program, time management). Facilitators will also have access to the Facilitator Portal (access restricted to certified TIK facilitators), which includes several supplementary tools to improve the program’s delivery. To evaluate whether TIK is delivered as intended and facilitate comparisons across groups, both facilitators and an observer element (who will be present in all groups delivered during the trial) will complete the TIK Program Fidelity Checklist at the end of each session. For each planned topic and activity, they will indicate if it was covered or not, with space provided for additional comments. Facilitators will make an effort to deliver any content missed in a given session in the session that follows. Facilitators will not be blinded to the participants’ condition.

## Measures

### Sociodemographic measures

A questionnaire specifically developed for this study will collect sociodemographic and health-related data at baseline, referring to the parents (i.e., sex, education, nationality, ethnicity, professional status, marital status, if currently in a marital relationship with the other child’s parent, monthly family income, receipt of financial support from public entities or others, perceived sufficiency of household income, receipt of support from social services, household size, history of MH problems) and the child (i.e., sex, age, and existence of mental, physical and/or developmental problem).

### Psychosocial risk

Psychosocial risk data will be collected through the sociodemographic questionnaire described above. A composite score will be computed by summing up the following risk conditions: (1) parental low education (≤ 9 years); (2) ethnic minority (non-White), (3) parental unemployment (currently or in the previous 12 months); (4) single-parent family, (5) low monthly family income (< 2 minimum national salaries); (6) parental receipt of financial support from public entities or others (yes v. no); (7) parental perception of insufficient household income to meet daily family needs (yes v. no), (8) parental receipt of support from social services (e.g., child protection services; yes v. no); (9) high household size (≥ 75th percentile of the sample distribution); (10) parental previous diagnosis of MH problems (yes v. no); and (11) child previous diagnosis of physical or developmental problems (yes v. no). The presence of each risk condition will be coded as 1 and absence will be coded as 0. Scores can range between 0 and 11 and higher scores reflect higher psychosocial risk.

### Outcome measures

Outcome measures will be assessed with the Portuguese Versions (PV) of the following instruments at specific time points (see Table 1).

### Primary outcome measures

#### Parental emotion socialization

##### Coping with Children’s Negative Emotions Scale (CCNES)

A modified version of the CCNES ([53]; PV: [54, 55]) will be used to assess parents’ emotion socialization behaviors. The scale consists of 12 hypothetical scenarios in which the child experiences a negative emotion (e.g., anger, sadness). For each scenario, parents rate their likelihood of responding in each of seven ways on a 7-point Likert scale, ranging from 1 (*very unlikely*) to 7 (*very likely*). The measure includes seven subscales: Emotion-Focused, Problem-Focused, Minimizing, Punitive, Expressive Encouragement, Distress, and Ignoring reactions. In the present study, items from the Distress subscale were reworded to enhance clarity, and the Ignoring subscale was included, following [56]. Items from the Minimizing, Punitive, Distress, and Ignoring subscales are summed to assess emotion dismissing responses (i.e., negative reactions), and items from the Emotion-Focused, Problem-Focused, and Expressive Encouragement subscales are summed to measure emotion coaching (i.e., positive reactions). A total score can be obtained for each scale by averaging the items (range 1–7). Higher scores in each of these categories indicate greater endorsement of that practice. In the Portuguese version, Cronbach’s alpha ranged from 0.83 to 0.89 [55].

##### Parents’ Beliefs About Children’s Emotions Questionnaire (PBACE)

The PBACE ([57]; PV: [58]) is a self-report measure designed to assess parents’ beliefs about children’s emotions (e.g., “*Showing anger is not a good idea for children*”). The questionnaire consists of 33 items rated on a 6-point Likert-type scale, with responses ranging from 1 (*strongly disagree*) to 6 (*strongly agree*). In the present study, four subscales will be used: Value of Anger (6 items; belief that anger can be valuable), Manipulation (4 items; belief that children’s emotional expression can be used to manipulate others), Control (5 items; belief that children can regulate their emotions), and Autonomy (7 items; belief that children should manage their emotions independently). Total scores will be computed for each of these subscales by averaging the respective items (range 1–6), with higher scores reflecting stronger endorsement of the corresponding belief in that category. In the Portuguese version, Cronbach’s alpha was 0.90 [58].

##### Interpersonal Mindfulness in Parenting scale (IM-P)

The subscale Self-regulation in Parenting of the IM-P ([59]; PV: [60]) will be used to assess parents’ ability to regulate their own emotions and behaviors in the parenting context. It is composed of 8 items (e.g. “*When I am upset with my child*,* I notice how I am feeling before I take action*”) rated on a 5-point Likert-type scale from 1 (*never true*) to 5 (*always true*). A total score will be obtained by summing up the items (range 8–40; items 1, 4, 5 and 8 will be first reverse-scored). In the Portuguese version, Cronbach’s alpha for this subscale was 0.83 [60].

##### Difficulties in Emotion Regulation Scale - Short Form (DERS-SF)

The DERS-SF ([61]; PV: [62]) is an 18-item self-report measure of difficulties in emotion regulation (e.g., “*I am confused about how I feel*”). Items are rated on a 5-point Likert-type scale ranging from 1 (*almost never*) to 5 (*almost always*). A total score (range 1–5) is obtained by averaging all items, with higher scores indicating greater difficulties. In line with the recommendations of the Portuguese authors [62], items 1, 4 and 6 will be excluded from the analyses. In the Portuguese version, Cronbach’s alpha was 0.93.

### Secondary outcome measures

#### Children

##### Strengths and Difficulties Questionnaire - Parent (SDQ-P)

The SDQ-P ([63]; PV: [64]) is a brief screening instrument designed to assess children’s emotional and behavioral difficulties. The parent-report version consists of 25 items (e.g., “*kind to younger children*”), each rated on a 3-point Likert-type scale, from 0 (*not true*) to 2 (*certainly true*), based on the child’s behavior over the past 2 months. Items 7, 11, 14, 21 and 25 are reverse-scored. The *Total difficulties* score (range 0–40) is calculated by summing the following subscales: Internalizing Problems and Externalizing Problems. Higher scores indicate greater difficulties. The Prosocial Behaviors subscale (range 0–10) is scored separately, as a measure of strength. Two versions of the scale (2–4 years old and 4–17 years old) will be presented to parents as a function of the child’s age. The scales differ slightly on items 18, 21 and 22 to ensure age-appropriate language. In the Portuguese version, internal consistency was acceptable for all subscales: Internalizing Problems: *α* = 0.72, Externalizing Problems: *α* = 0.79, Prosocial Behaviors: *α* = 0.70 [65].

#### Emotion Regulation Checklist (ERC)

The ERC ([66]; PV: [67, 68]) is a self-report measure to assess children’s emotion regulation competencies. The revised PV of the scale [68] consists of 20 items rated on a 4-point Likert-type scale, ranging from 1 (*never*) to 4 *(almost always*). The instrument includes two subscales: the Emotion Regulation (7 items), which assesses children’s emotional expression, empathy and self-awareness (e.g., “*is easily frustrated*”) and the Emotion Lability/Negativity (13 items), which measures children’s reactivity to negative emotions and emotional intensity (e.g., “*exhibits wide mood swings*”). Items 5, 9, 16 and 18 are reverse scored. For each subscale, a total score is obtained by the sum of the corresponding items (range 7–28 and 13–52, respectively). Higher scores on the Emotion Regulation scale reflect better emotion regulation, whereas higher scores on the Lability/Negativity scale indicate greater difficulties in emotion regulation. In the Portuguese version, Cronbach’s alphas ranged between 0.66 and 0.80 [68].

#### Parents

##### Parental Stress Scale (PSS)

The PSS ([69]; PV: [70]) is a self-report scale comprising 18 items to assess stress experienced by parents in relation to raising their children (e.g., “*I am happy in my role as a parent*”). Following the recommendations from the Portuguese version (Algarvio et al., 2018), items 1–2 and 17–18 will be excluded from the analyses. Responses are provided on a 5-point Likert-type scale from 1 (*strongly disagree*) to 5 (*strongly agree*). A total score (range 14–70) is calculated by summing all items, with items 5–8 being reverse-scored. Higher scores reflect greater levels of parenting stress. In the Portuguese version, Cronbach’s alpha was 0.76 [71].

##### Hospital Anxiety and Depression Scale (HADS)

The Depressive Symptoms subscale of the HADS ([72]; PV: [73]) will be used to measure parental depressive symptoms experienced over the past week. This self-report subscale consists of 7 items (e.g., “*I feel cheerful*”) rated on a 4-point Likert-type scale, with scores ranging from 0 to 3 (e.g., “*not at all*”, “*most of the time*”). The total score (range 0–21) is obtained by summing up the items, with higher scores indicating greater levels of depressive symptoms. In the Portuguese version, Cronbach’s alpha was 0.89 [74].

##### Me as a Parent Questionnaire (MaaP)

The Self-Efficacy subscale of the MaaP ([75]; PV: [76]) will be used to assess parents’ self-efficacy in parenting. The subscale has 4 items (e.g., “*My parenting skills are effective*”), rated on a 5-point Likert-type scale, from 1 (*strongly disagree*) to 5 (*strongly agree*). A total score is obtained by summing up the items (range 4–20), with higher scores reflecting higher perceptions of parenting self-efficacy. In the Portuguese version, the Cronbach’s alpha for this subscale was 0.78 [77].

### Other outcome measures

#### Feasibility of the intervention

TIK’s feasibility will be evaluated in terms of implementation fidelity, adherence to the intervention and facilitators and barriers to TIK implementation. Adherence will be estimated through the number of sessions attended; those who attend at least four of the six sessions will be considered completers (67%), the remaining will be considered non-completers. Participants will be asked to answer two questions on facilitators and barriers to TIK implementation at post-intervention (*What factors made it easier for you to participate in the program? What factors made it more difficult for you to participate in the program?*). When applicable, the time of the dropout from the intervention will also be recorded (e.g., after session 4, 5, 6 or at follow-up).

#### Acceptability of the intervention

TIK’s acceptability will be evaluated at the end of the program. Participants will be asked to complete a questionnaire composed of 16 questions answered on a Likert-type scale ranging from 1 (*not at all*) to 5 (*very much*), covering: (a) overall satisfaction with TIK; (b) if TIK meets parents’ expectations and contributes to improvements in their confidence as parent, in their relationship with their children, in their children well-being, and in their capacity to understand their children’s emotions and how to manage them; (c) the frequency to which they apply TIK contents on their daily interactions with their children; (d) the adequacy of the number, frequency and length of the sessions; (e) satisfaction with the group format; (f) perception of TIK’s facilitators competence and intervention’s facilities; and (g) usefulness of acquired strategies for parenting in the long-term. Participants will also be asked to report if they would recommend the program to other parents on a yes/no scale, as well as to rate the degree of facility/difficulty in understanding the concepts of emotion coaching and in applying emotion coaching strategies on a daily basis, using a Likert-type scale ranging from 1 (*very easy*) to 5 (*very difficult*). They will also be asked to answer three open-ended questions to report on the most and least useful aspects of the program, and if there were other contents that they would like to address in the program. A last open-ended question inquires about other suggestions for improving TIK.

### Harms

TIK has been investigated and applied worldwide and has been translated into 15 languages [10], and no risks or adverse effects have been documented to date (e.g. [12, 51]), . The facilitators will monitor participants’ well-being across the group sessions through open-ended questions made individually (separately from the group) after sessions 2, 4, and 6. Participants who missed one session will receive a phone call from the facilitators to monitor reasons for the missed session and inquire about well-being.

### Data management

Data management of this clinical trial will follow Lusófona University’s data protection policies and the General Data Protection Regulation (GDPR - UE, 2016/679). Research assistants will be responsible for data collection and data entry. Data from paper questionnaires will be entered on REDCap. By including range checks, field validation, mandatory fields, logic rules, and indicators of missing values, among other features, REDCap allows enhancing data quality in terms of its accuracy, completeness, and reliability. To maximize data accuracy, two independent research assistants will enter the same paper questionnaires into REDCap, which will compare the two entries and signal any discrepancy. Paper questionnaires will be kept at Lusófona University (access restricted), and any identifying data will be removed. Each participant will receive an ID code that would allow pairing data across assessment points. Pseudonymized data will be stored at Lusófona University server, after being encrypted and accessed by password, as well as signed consent forms. Only research assistants and project coordinators will have access to the data. Participants will have the right to access, change, or delete their own data at any time, as well as to remove their consent for participation, with no need for explanations. Data will be maintained for the time strictly necessary for achieving this project’s aims.

### Statistical methods

#### Process evaluation

Descriptive statistics (mean ± standard deviation and frequencies) will be computed for each item of the acceptability questionnaire using the Statistical Package for the Social Sciences (SPSS, IBM Corp., v.30.0). Responses to the open-ended questions of this questionnaire, as well as those referring to facilitators and barriers to TIK implementation, will be examined through thematic analysis following a deductive–inductive approach informed by the stepwise framework proposed by Braun and Clarke [78].

#### Efficacy evaluation

The statistical analyses will be carried out using SPSS and the R software (version 4.4.0). The level of statistical significance will be set at *p* < .05. Descriptive statistics will be computed for all study variables. Pearson/Spearman correlations will be conducted to explore associations between all the study variables at each assessment wave. Pre-test differences between the intervention and control groups will be analyzed regarding sociodemographic and health characteristics (using qui-square tests) and the primary and secondary outcomes using t-tests (for dichotomous independent variables) and one-way ANOVAs (for categorical and ordinal independent variables) to identify potential covariates.

Linear mixed-effects models accounting for repeated measures within participants will be tested to analyze TIK’s efficacy. Time 0 will be defined as the date of the pre-test assessment, time 1 will be the date of the post-test, and time 2 will be the date of the follow-up assessment. Time, group conditions (intervention (coded as 1) vs. control (coded as -1)), and the 2-way interaction time x group conditions will be included in the models as fixed effects. Moreover, for children-related outcomes (i.e., children’s emotional and behavioral functioning), the child will be treated as the primary unit of analysis and models will also include a random intercept and a random slope for time at the child level in order to account for between-child variability in baseline (at pre-test) levels of the outcome variables and between-child variability in change across time. Since both parents may participate in the study, the child-level random effects also allow one to take into account the non-independence of both parents’ reports for the same child. For parents-related outcomes (i.e., parental emotion socialization and parents’ emotional and behavioral functioning), the parent will be treated as the primary unit of analysis and models will include a random intercept and a random slope for time at the parent-level to account for between-parent variability. To account for the nesting of both parents within the same family, a random intercept at the child level will be included.

Exploratory moderation analyses will be performed in order to examine whether pre-test psychosocial risk is a moderator of TIK’s efficacy. Psychosocial risk, the 2-way interaction time x psychosocial risk, the 2-way interaction group conditions x psychosocial risk, and the 3-way interaction time x group conditions x psychosocial risk will be added to the previous linear mixed-effects models as fixed effects. Significant interactions with the continuous predictor (i.e., psychosocial risk) will be interpreted and graphed using one standard deviation above and below the grand mean as high and low values.

All linear mixed-effects models will be estimated using maximum likelihood, and the models’ assumptions will be validated by analyzing residual graphs. Deviance difference tests will be performed between a baseline growth model with only time as a fixed effect and models with the predictors to examine model fit improvements. All models will be adjusted for the covariates identified in the preliminary analyses. One model per outcome variable will be performed. Effect size measures will be calculated, namely the ICC (intraclass correlation coefficient) for random effects and Cohen’s *f*^2^ for fixed effects, following the guidelines of Lorah [79]. These analyses, including the calculation of the effect sizes, will be performed using the package *lme4* from R.

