## Objectives

Framed within the Getting To Outcomes framework [39], this trial aims to conduct a process and efficacy evaluation of TIK among parents of preschool aged children in Portugal. Regarding process evaluation, we will evaluate TIK’s (a) feasibility (e.g., adherence to the program, whether TIK is implemented as intended and enablers and barriers to TIK implementation), and (b) acceptability (e.g., satisfaction, suggestions for improvement). Regarding efficacy, we will assess whether the TIK will be able to improve parental emotion socialization (primary outcomes, e.g., parents’ reactions to children’s emotions, parental emotion regulation) and parents’ and children’s emotional and behavioral functioning (secondary outcomes, e.g., parenting stress, children’s emotional/behavioral problems). A waiting list control group will be used. We hypothesize that parents receiving TIK will (1) show improvements in parental emotion socialization and (2) report improvements in parental and children functioning, across time (i.e., from pre-intervention to follow-up), compared with parents of the waiting list control group. We will also explore whether families’ psychosocial risk moderate the TIK’s efficacy on primary and secondary outcomes.

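### Eight co-equal primary scores are each tested at p < .05, with no lead score, no stated multiplicity rule, and no statement of how many must succeed to support hypothesis 1

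*Protocol article*

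**What the plan says.** Hypothesis 1 (Objectives) is that parents receiving the programme will "show improvements in parental emotion socialization" relative to the waiting list. This is a claim about a domain, not about one score.

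Under Primary outcome measures the domain is measured as follows:

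- **CCNES:** four subscales form a dismissing composite; for the other composite, "items from the Emotion-Focused, Problem-Focused, and Expressive Encouragement subscales are summed to measure emotion coaching". Two scores.
- **PBACE:** "In the present study, four subscales will be used", each with its own average and no overall total. Four scores.
- **IM-P:** one self-regulation subscale score.
- **DERS-SF:** one total score.

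Table 1 lists the four instruments as primary without ranking them.

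Under Efficacy evaluation, "The level of statistical significance will be set at" p < .05, "the 2-way interaction time x group conditions will be included in the models as fixed effects", and "One model per outcome variable will be performed". The Sample size section gives about 132 participants for 80% power at alpha 0.05 for the time x group interaction, and about 152 to be recruited. The article labels only the psychosocial-risk moderation and the complier analysis as exploratory.

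**The concern.** Eight separate tests at 0.05 bear on one hypothesis, and the article gives no rule for combining them. Followed as written, it would let a single significant subscale be presented as a positive primary result. The error behind that claim would exceed the 5% used in the power statement.

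The risk is sharpened by the setting. The trial is open-label and all eight scores are parent self-reports, so no blinded or objective measure checks selective emphasis on one favourable score. The article also plans to share preliminary or partial results while the trial runs (Patient and public involvement; Data and trial monitoring). A lead score chosen late could therefore be influenced by data.

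**Working it through.** **Count of primary scores.** 2 (CCNES) + 4 (PBACE) + 1 (IM-P) + 1 (DERS-SF) = 8.

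**The plan's own sample size.** The effect is described only as medium-sized and the random-effect variances are not given, so 132 cannot be reproduced exactly. As a benchmark, a two-group comparison with an assumed d = 0.5, 80% power and two-sided 0.05 needs 126 in total (normal approximation) or 128 (t-test). At 66 per arm its power is 81–82%. The stated figure is thus close to what one test at alpha 0.05 needs. The recruitment target matches 132 × 1.15 = 151.8, or 152. Nothing below depends on these details.

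**Assumptions for the error rate.** One time x group test per score, two-sided 0.05 (sidedness is not stated), all eight nulls true, and any one significant score counted as support. Correlations between scores are not given, so a range is shown.

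Independent scores, either direction: 1 − 0.95^8 = 0.337.

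Independent scores, beneficial direction only: 1 − 0.975^8 = 0.183.

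For a common correlation ρ, with scores oriented so that benefit is positive and c = 1.96, the rate in either direction is

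1 − ∫ [Φ((c − √ρ·u)/√(1−ρ)) − Φ((−c − √ρ·u)/√(1−ρ))]^8 φ(u) du.

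Dropping the second Φ term gives the beneficial-direction rate.

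| ρ | At least one p < .05, either direction | Beneficial direction only |
|---|---|---|
| 0 | 33.7% | 18.3% |
| 0.3 | 30.0% | 15.2% |
| 0.5 | 25.0% | 12.5% |
| 0.7 | 19.1% | 9.5% |

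A single two-sided test gives 5% and 2.5% respectively.

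**Direction of the PBACE scores.** The article does not say which direction is beneficial for these four subscales. If either direction were read as support there, and only the beneficial one for the other four scores, the independent-case rate is 1 − 0.95^4 × 0.975^4 = 1 − 0.8145 × 0.9037 = 0.264. This lies between the two columns.

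**Power if all eight are adjusted.** Power of 80% at 0.05 corresponds to a noncentrality of 1.960 + 0.842 = 2.802. Bonferroni over eight uses 0.05/8 = 0.00625, critical value about 2.734. Power per score is Φ(2.802 − 2.734) ≈ 0.53. Restoring 80% would need 132 × ((2.734 + 0.842)/2.802)^2 ≈ 215.1, so 216 analysed, and 216/0.85 gives 255 recruited.

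**If all eight had to succeed.** With 80% power for each and independence, power is 0.8^8 ≈ 17%, and higher with correlation. Neither the any-one nor the all-eight reading combines 80% power with 5% error.

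**The case against.** The strongest objection is that silence is not a decision. A nominal p < .05 is compatible with a hierarchical or Holm rule in an analysis plan that is not shown, and the article never says that p-values will be unadjusted or that one positive score suffices. This stands in part: a reader might infer that the trial has no multiplicity control, but the document supports only that none is stated here. It does not remove the point. Which score is primary, and what the sample size refers to, are protocol decisions, and the article fixes eight equal primaries against power for one test. An adjustment across all eight, added elsewhere, would not fit that power statement.

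A reader might also infer that hypothesis 1 would be falsely claimed one time in three to four. That is the either-direction rate. Hypothesis 1 is about improvement, so a significant worsening would not support it. The rate also falls below one in four once the correlation exceeds about 0.5. Such correlations are possible, because all scores come from the same parent and two of them concern parental emotion regulation.

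Finally, a reader might count 13 primary scores by taking the seven CCNES subscales separately. The CCNES section says that an averaged score can be obtained for each scale, but it sums the subscales into two composites and does not commit to seven tests. Eight is the supported count.

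**Conclusion.** The point holds in this form: eight equal primary scores, a separate model for each at p < .05, and no stated lead score, multiplicity rule or success criterion for hypothesis 1, alongside a sample size that covers one test.

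If any one significant score is taken as support and all eight nulls are true, the chance of at least one p < .05 is about 34% under independence, 25% at correlation 0.5 and 19% at 0.7. For beneficial results only, it is about 18% and 13% at correlations 0 and 0.5, or roughly five to seven times the 2.5% of a single two-sided test. Because the PBACE directions are unstated, the true figure may lie between the two sets. The any-one rule and the correlations are assumptions; the article gives neither. The rate is above nominal at every correlation examined.

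**What to change.** Before outcome data are analysed:

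1. Name one confirmatory primary score, at the sponsor's choice, and one time x group contrast (the slope, or a stated time point), tested at 0.05. Naming a time point alone is not enough, because the planned test is an interaction over three assessments.
2. Test the other seven in a fixed order or with Holm, and state the beneficial direction of each, including the four PBACE subscales. To keep error over all eight at 5%, start these tests only if the lead test succeeds.
3. Report all eight whatever the result.
4. State that the 80% power at 132 is for a single test at alpha 0.05, that is, for the named score. If Bonferroni over all eight is preferred, state that power per score is about 53% at that size.

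The cost is wording, an amendment through the ethics procedure that the article describes, and bringing the registry entry into line if it differs (it is not shown). No extra participants are needed if one lead score is named. The downside is that fewer scores can carry a confirmatory claim.
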